# The EUPHRATES trial (Evaluating the Use of Polymyxin B Hemoperfusion in a Randomized controlled trial of Adults Treated for Endotoxemia and Septic shock): study protocol for a randomized controlled trial

**DOI:** 10.1186/1745-6215-15-218

**Published:** 2014-06-11

**Keywords:** Endotoxin, Endotoxemia, Septic shock, Polymyxin-B, Hemoperfusion, Theragnostics

## Abstract

**Background:**

Septic shock is common and has unacceptably high morbidity, mortality, and associated cost with numerous failed attempts at developing effective therapies. Endotoxin, one of the most potent mediators of sepsis, is found in high levels in approximately 50% of patients with septic shock. Polymyxin B (PMX) hemoperfusion has been shown in numerous studies to successfully remove endotoxin and potentially improve outcomes. EUPHRATES (Evaluating the Use of Polymyxin B Hemoperfusion in a Randomized controlled trial of Adults Treated for Endotoxemia and Septic shock) is a theragnostic trial (matching blood measurement to treatment capability) of PMX hemoperfusion in patients with septic shock and confirmed endotoxemia as measured by the endotoxin activity assay (EAA).

**Methods:**

EUPHRATES is a pivotal regulatory trial that is multi-centered, placebo-controlled and blinded. The trial is being conducted in fifty ICUs in the United States and Canada and is powered to enroll 360 patients. Patients with persistent septic shock despite adequate fluid resuscitation on vasopressors for more than 2 and less than 30 hours are eligible for measurement of the EAA. Those with EAA ≥0.60 are eligible to be randomized to treatment with two sessions of PMX hemoperfusion 24 hours apart. The primary endpoint for the trial is 28-day all-cause mortality.

**Discussion:**

Unique features of the trial include absence of systemic inflammatory response (SIRS) criteria as a requirement for inclusion, use of the EAA to confirm endotoxemia as a requisite for treatment, and use of a detailed “façade” hemoperfusion event as a blinding mechanism. The outcomes of the second interim analysis included a resizing of the trial to 650 patients and the addition of an exclusion criterion of subjects with multiple organ dysfunction score (MODS) ≤ 9. Results are anticipated in 2016.

**Trial registration:**

Clinicaltrials.gov identifier: NCT01046669. Registered: January 8, 2010.

## Background

Despite great advances in our understanding of the pathophysiology of severe sepsis (sepsis associated with organ dysfunction) and septic shock (severe sepsis associated with need for vasopressors following adequate fluid resuscitation), attempts to translate these findings into novel treatments and improved outcomes for patients have been disappointing
[1]. Mortality, morbidity, and costs associated with management of septic shock patients in ICUs are unacceptably high
[2]. Even the most promising of potential new therapies targeting specific mediators of the host response have failed to demonstrate consistent benefit when tested in large multi-centered, randomized, controlled trials despite encouraging results in animals and earlier phase studies
[3]. Reasons cited for these failures are wide ranging, but likely include poor patient selection for therapies due to the heterogeneous and syndromic definition of the disease state of sepsis using American College of Chest Physicians / Society of Critical Care Medicine consensus criteria as well as failure of these therapies when subjected to the design rigors and mandated mortality outcomes found in late phase regulatory pathway trials
[4].

Endotoxin (lipopolysaccharide; LPS) is perhaps the best studied and one of the most potent initiators and mediators of the host response in sepsis. Studies measuring endotoxin levels in septic patients have consistently demonstrated three key findings. First, a dose-response relationship between endotoxin levels in septic patients and adverse outcomes including organ failure and death
[5]; second, the presence of elevated levels of circulating endotoxin in some, but not all, patients with sepsis including some with Gram positive infections and other forms of sepsis likely through the mechanism of gut translocation
[5,6]; and third, the persistence of endotoxemia often days into the course of the disease process of severe sepsis
[7]. A variety of approaches have been tried to target endotoxin therapeutically including monoclonal antibodies to neutralize LPS, small molecule and other competitive inhibitors of the LPS receptor Toll-like receptor (TLR)4 to block LPS signaling, use of specific molecules to enhance endotoxin deactivation and clearance, and extracorporeal devices to remove endotoxin
[8]. In 1982, Ziegler and colleagues
[9] first reported the successful treatment of a cohort of patients with Gram negative bacteremia and shock using a human anti-serum raised against the *Eschericia Coli* J5 bacterium core LPS or endotoxin. A 17% absolute reduction in death was observed in a selected group of 212 patients
[9]. Of note, a very high percentage of these subjects had Gram negative bacteremia (63%), anticipated to correlate very highly with the presence of endotoxemia. Subsequently, two large projects both testing monoclonal antibodies targeting LPS in sepsis, HA-1A and E5, each demonstrated positive results in early phase studies
[10,11] including a 1991 Ziegler and colleagues study
[11] again demonstrating a 19% reduction in mortality in the subset of 200 patients with Gram negative bacteremia treated with HA-1A in a total sample of 543 patients. However, several large follow-up randomized controlled trials with both HA-1A as well as E5 were negative and neither drug was approved for clinical use in the United States
[12,13]. More recently, additional attempts at neutralizing endotoxin to increase survival in severe sepsis utilizing (a) bactericidal/permeability-increasing protein, (b) a lipid emulsion of recombinant HDL that binds endotoxin, (c) a small molecule TLR4 inhibitor (TAK242), and (d) E5564, a lipid A analogue and competitive inhibitor of TLR4, also all failed to show reduction in mortality in severe sepsis patients
[14-16].

Polymyxin B (PMX) is a cyclic cationic polypeptide antibiotic derived from *Bacillus polymyxa* that has the ability to bind and neutralize endotoxin. Unfortunately, infusion of polymyxin in humans results in nephrotoxicity and neurotoxicity limiting its intravenous use to salvage therapy for Gram negative enterobacteriaciae resistant to other antibiotics
[17]. A novel therapeutic strategy whereby PMX is adsorbed to a polystyrene fiber in a hemoperfusion device that is used to remove circulating endotoxin was developed in Japan in the late 1990s. A wide variety of small open-label clinical trials using this strategy in sepsis and other patient subtypes have been published with generally encouraging results. Cruz and colleagues
[18] published a systematic review and meta-analysis of 28 trials using PMX direct hemoperfusion (PMX-DHP) to treat patients with severe sepsis and septic shock. Although there was heterogeneity amongst the trials largely done in Europe and Japan, across a total cohort of 978 patients treated with the therapy, improvements were noted in hemodynamics (mean arterial pressure) as well as oxygenation (PaO2/FiO2 ratio, and there was a statistically significant improvement in risk of death (risk ratio 0.53, 95% CI 0.43 to 0.65)
[18]. More recently, in 2009, the Early Use of Polymyxin Hemoperfusion in Abdominal Septic Shock (EUPHAS) trial
[19], a randomized but unblinded study of 64 patients in 10 tertiary Italian ICUs, demonstrated statistically significant improvements in the primary endpoints of hemodynamics and organ dysfunction. Also, the absolute risk of death at 28 days improved significantly from 53% in the conventional therapy group to 32% in the PMX-DHP treated group
[19]. This result, albeit encouraging, is considered controversial as the trial was stopped early after an interim analysis showed the mortality difference in a secondary endpoint. In addition, the trial was not blinded
[20]. Patients were selected for therapy based on evidence of septic shock from an intra-abdominal source to hopefully enrich the patient population, but endotoxin levels were not measured prior to enrollment - a common theme in all the previously discussed trials attempting to neutralize endotoxin with drug therapy. Thus, there have been widespread calls for a definitive randomized controlled trial on this promising but not widely accepted therapy in North America
[20].

Here, we present the protocol for, and discuss the design, of the “Evaluating the Use of Polymyxin B Hemoperfusion in a Randomized controlled trial of Adults Treated for Endotoxemia and Septic shock (EUPHRATES)” trial. We believe it to be the first blinded and randomized controlled, diagnostic-directed trial of a hemoperfusion device ever done in sepsis. We hypothesize that targeted treatment of patients with septic shock and high levels of circulating endotoxin as confirmed by the endotoxin activity assay (EAA) combined with directed therapy in the form of PMX-DHP endotoxin removal, will result in a significant reduction in 28-day all-cause risk of death.

## Methods and design

### Study design and outcomes

The ongoing EUPHRATES trial (Clinicaltrials.gov identifier: NCT01046669) is a North American pivotal (under Investigational Device Exemption (IDE) from the United States Food and Drug Administration (FDA)) double-blinded theragnostic trial of PMX-DHP therapy in adult patients with septic shock and confirmed endotoxemia as measured by EAA. The trial began in June 2010 and is scheduled to be completed by the end of 2016. Ethics approval for the trial protocol has been obtained from the research ethics board responsible for each site prior to starting the trial. A list of all ethical bodies that reviewed and approved the trial is listed in Table 
1. The primary outcome of the trial is 28-day all-cause mortality. The total number of patients estimated to be included in the study was planned as 360 from 50 ICUs in the United States and Canada. Consecutive patients with evidence of septic shock as indicated by initiation of intravenous antibiotics and on vasopressor therapy for hypotension will be screened and those eligible will be consented for a blood draw for measurement of EAA. The consort diagram is shown in Figure 
1. Those with an EAA ≥0.60 (high endotoxin activity level) will be considered eligible and consented for randomization to potential treatment with PMX-DHP or the control group. Otherwise, eligible patients with an EAA <0.60 after up to two blood draws 4 to 6 hours apart will be not be randomized but will be followed using a minimal dataset for mortality at 28 days in an observational cohort study. It is estimated that approximately 50% of otherwise eligible patients will have an EAA ≥0.60. Table 
2 summarizes the inclusion and exclusion criteria for EUPHRATES. Note that a patient with any type of infection producing septic shock is eligible to be enrolled if high endotoxin activity is present (EAA ≥0.60) as endotoxemia is not limited to Gram negative infection only (likely gut-derived endotoxin from translocation in non-Gram negative bacterial shock). In addition to the primary outcome measure of 28-day all-cause mortality, secondary outcomes include 90-day, 6-month and 1-year all-cause mortality. Hemodynamic outcomes will be followed using the cumulative vasopressor index (Table 
3) and other organ failure outcomes will be captured as both total and component scores of the multiple organ dysfunction score (MODS)
[21,22]. Renal outcomes will be tracked using the Acute Kidney Injury (AKIN) criteria
[23]. A full list of secondary and exploratory objectives is listed in Table 
4.

**Table 1 T1:** Institutional Review Board information for EUPHRATES

**Figure 1 F1:**
[figure not shown]
**Consort diagram for EUPHRATES (Evaluating the Use of Polymyxin B Hemoperfusion in a Randomized controlled trial of Adults Treated for Endotoxemia and Septic shock trial).** EAA, endotoxin activity assay.

**Table 2 T2:** Summary of inclusion and exclusion criteria

**Inclusion criteria**	**Exclusion criteria**
Subjects who meet the following criteria (and have a signed informed consent) will be allowed into the study:	1. Inability to obtain an informed consent from the subject, family member or an authorized surrogate
1. Age ≥18 years of age	2. Lack of commitment for full medical support
2. Hypotension requiring vasopressor support: Requirement for at least one of the vasopressors listed below, at the dose shown below, for at least 2 continuous hours and no more than 30 hours	3. Inability to achieve or maintain a minimum mean arterial pressure of ≥65 mmHg despite vasopressor therapy and fluid resuscitation
a. Norepinephrine >0.05 μg/kg/minute	4. Subject has end-stage renal disease and requires chronic dialysis
b. Dopamine >10 μg/kg/minute	5. There is clinical support for non-septic shock such as
c. Phenylephrine >0.4 μg/kg/minute	a. Acute pulmonary embolus
d. Epinephrine >0.05 μg/kg/minute	b. Transfusion reaction
e. Vasopressin >0.03 units/minute	c. Severe congestive heart failure (for example, New York Heart Association Class IV, ejection fraction <35%)
f. Vasopressin (any dose) in combination with another vasopressor listed above	6. Subject has had chest compressions as part of cardiopulmonary resuscitation this hospitalization without immediate return to communicative state
3. The subject must have received intravenous fluid resuscitation of a minimum 30 mL/kg administered within 24 hours of eligibility	
4. Documented or suspected infection defined as definitive or empiric intravenous antibiotic administration	7. Subject has had an acute myocardial infarction within the past 4 weeks
5. Endotoxin activity assay ≥0.60	8. Subject has uncontrolled hemorrhage (acute blood loss requiring >3 Units of Packed red blood cellsin the past 24 hours)
6. Evidence of at least one of the following criteria for new onset organ dysfunction that is considered to be due to the acute illness	9. Major trauma within 36 hours of screening
a. Requirement for positive pressure ventilation via an endotracheal tube or tracheostomy tube	10. Subject has severe granulocytopenia (leukocyte count <500 cells/mm^3^) or severe thrombocytopenia (platelet count <30,000 cells/mm^3^)
b. Thrombocytopenia defined as acute onset of platelet count <150,000 μ/L or a reduction of 50% from prior known levels	11. HIV infection in association with a last known or suspected CD4 count of <50/mm^3^
c. Acute oliguria defined as urine output <0.5 ml/kg/hour for at least 6 hours despite adequate fluid resuscitation	12. Subject’s baseline state is non-communicative
	13. Subject has sustained extensive third-degree burns within the past 7 days
	14. Body weight <35 kg
	15. Known hypersensitivity to polymyxin B
	16. Subject has known sensitivity or allergy to heparin or has a history of heparin associated thrombocytopenia
	17. Subject is currently enrolled in an investigational drug or device trial
	18. Subject has been previously enrolled in the current trial
	19. Any other condition, that in the opinion of the investigator, would preclude the subject from being a suitable candidate for enrolment, such as end stage chronic illness with no reasonable expectation of survival to hospital discharge
	20. Multiple Organ Dysfunction Score ≤9 ** - *added post-second interim analysis*

**Table 3 T3:** Cumulative vasopressor index

**Vasopressor**	**Dose Range**	**Dose Range**	**Dose Range**	**Dose Range**
	**1 point**	**2 Points**	**3 Points**	**4 Points**
Dopamine	0 dose ≤ 5	5 < dose ≤ 10	10 < dose ≤ 15	> 15
(mcg/kg/min)				
Epinephrine	-	0 < dose < 0.05	0.05 < dose < 0.1	> 0.1
(mcg/kg/min)				
Norepinephrine	-	0 < dose < 0.05	0.05 < dose < 0.1	> 0.1
(mcg/kg/min)				
Phenylephrine	-	0 < dose < 0.4	0.4 < dose < 0.8	> 0.8
(mcg/kg/min)				
Vasopressin	-	-	-	Any dose
(units/min)				

**Table 4 T4:** Secondary and exploratory outcomes

1.	To compare mortality between the two groups at 90 days, 6 months and 12 months post-start of treatment
2.	To compare the change in endotoxin levels between the PMX cartridge-treated group and the control group at 12 hours after completion of a second PMX cartridge, with a treatment target of ≥15% reduction of EAA levels with PMX cartridge treatment
3.	To compare the changes in vasopressor doses for the two groups from day 0 to day 3
4.	To compare the number of days of need for vasopressors in each group from day 0 to day 28 (days alive and off vasopressors)
5.	To compare changes in mean arterial blood pressure for the two groups from day 0 to day 3
6.	Comparison of the changes in renal function from day 0 to day 3:
i.	Fluid balance including urine output
ii.	Serum creatinine
7.	To compare the effects of two uses of the PMX cartridge on progression of, and recovery from, organ dysfunction using the multiple organ dysfunction score from day 0 to day 3
8.	To compare the number of days of need for renal replacement therapy in each group from day 0 to day 28 (days alive and off renal replacement therapy)
9.	To compare the number of days of need for mechanical ventilation in each group from day 0 to day 28 (days alive and off mechanical ventilation)
10.	To compare the mean number of days spent in hospital by subjects in each group for survivors to day 28
11.	To compare survival time from baseline to death within 28 days and compare the risk of death between the two study arms
12.	To compare survival time from baseline to death within 90 days and compare the risk of death between the two study arms

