#### Sample size and power

The power analysis is based on a two-sided Fisher’s exact test to compare the proportions of death within or at 28 days between the PMX treatment and control groups. It is assumed that for the control arm of standard medical care alone approximately 35% subjects will die by day 28 after the enrollment. It is also hypothesized that there will be an approximately 15% improvement in 28-day mortality rate for subjects randomized who receive the standard medical care plus the PMX cartridge, as compared to those receiving the standard medical care alone. The overall significance level for the entire sequence of primary efficacy tests is assumed at 5% in a two-sided test. An interim analysis based upon safety only was conducted after 76 patients were enrolled in January 2013. No efficacy analysis was conducted. The data safety monitoring board (DSMB) noted no specific safety concerns at that time. There is one planned additional interim analysis approximately at the midpoint (that is, 180 subjects enrolled). Because of the planned interim analysis, the maximum sample size for the trial (that is, if the trial is not terminated by the interim analysis) is based on the final efficacy test to compare day 28 mortality rate between the two study arms at a significance level of 0.048 based on the method of O’Brien and Fleming
[28].

Assuming a sample size ratio of 1:1 between the two study arms, a sample of 180 subjects per study arm (that is, a total of 360 subjects for both arms) provides at least 80% statistical power to detect the hypothesized effect size (that is, 15% difference) from the final primary efficacy test. The statistical power with the proposed sample size will thus be more than 80% from the entire sequence of the planned primary efficacy analyses. These power analyses assume a 15% attrition rate from the randomized subjects of each study arm. Therefore, a minimum of 306 evaluable subjects are necessary to achieve at least 80% statistical power based on the hypothesized effect size.

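### Hospital stay (Table 4, item 10) is compared only in survivors to day 28, so the comparison loses the protection of randomisation whenever the device changes who survives

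*Protocol article*

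**What the plan says.** Table 4 of the protocol article lists twelve secondary and exploratory outcomes. Item 10 is the only one on hospital stay: "To compare the mean number of days spent in hospital by subjects in each group for survivors to day 28". The restriction to survivors is part of the objective itself. The article gives no companion analysis of hospital stay in all randomised subjects. The ITT statements under Statistical analysis of results cover the primary endpoint and long-term survival, not this item.

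Under Study design and outcomes: "The primary outcome of the trial is 28-day all-cause mortality". Sample size and power assumes for the control arm that "approximately 35% subjects will die by day 28 after the enrollment", and that "there will be an approximately 15% improvement in 28-day mortality rate for subjects randomized".

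Three neighbouring items in Table 4 take another route. Items 4 (vasopressors), 8 (renal replacement) and 9 (ventilation) run from day 0 to day 28 and are not limited to survivors. Item 9, for example, counts "days alive and off mechanical ventilation".

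**The concern.** Randomisation makes the two arms comparable as randomised. It does not make the survivors of one arm comparable with the survivors of the other if treatment affects who survives. A device that works adds to the PMX survivor group patients who would have died on control, and the control survivor group has nobody to match them. A difference in mean stay between the two groups then mixes any effect on stay with a difference in who is being counted.

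What is at stake is how a secondary result of a pivotal trial is read. A mortality benefit could come with an apparently longer stay that no patient experienced, or a true shortening of stay could be hidden. If the extra survivors left early, the same mechanism would flatter the device.

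**Working it through.** **1. Reproduce the plan's figure, to settle the planning rates.** Inputs from Sample size and power: control mortality 35%; a 15% improvement; final two-sided significance level 0.048; power 80%; allocation 1:1; attrition 15%. Reading the improvement as 15 percentage points (35% to 20%):

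- The normal-approximation formula for two proportions gives 140 per arm, or 153 with continuity correction.
- 153 / 0.85 = 180 per arm, 360 in total, of whom 360 × 0.85 = 306 are evaluable. This matches the article.
- The exact power of Fisher's test at 153 per arm and level 0.048 is 0.805.

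A relative 15% reduction (35% to 29.75%) would need 1,300 per arm before attrition, so the absolute reading is the one planned. The article's own gloss agrees: "to detect the hypothesized effect size (that is, 15% difference) from the final primary efficacy test".

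**2. Share of PMX survivors without a control counterpart.** Let S0 and S1 be 28-day survival on control and PMX. Assume that nobody who would survive on control dies on PMX. Then

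share = (S1 − S0) / S1.

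With S0 = 0.65 and S1 = 0.80, survivors per 180 randomised are 180 × 0.65 = 117 and 180 × 0.80 = 144. The extra 27 are 27/144 = 18.75% of the PMX survivors.

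With a smaller benefit:
- S1 = 0.75: 0.10/0.75 = 13.3%.
- S1 = 0.70: 0.05/0.70 = 7.1%.

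The share does not depend on the sample size. At the resized total of 650 (325 per arm) and the same rates, survivors would be about 211 v 260 and the share would still be 18.75%.

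**3. Shift in the survivor-only mean.** Let the other survivors average m days in both arms and the extra survivors e days. The PMX survivor mean is [S0 × m + (S1 − S0) × e] / S1, so

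shift = share × (e − m).

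The values of e − m are assumptions:

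| PMX survival | Share | e − m = −4 | +5 | +10 |
|---|---|---|---|---|
| 80% | 18.75% | −0.75 | +0.94 | +1.88 |
| 75% | 13.3% | −0.53 | +0.67 | +1.33 |
| 70% | 7.1% | −0.29 | +0.36 | +0.71 |

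The entries are days added to the PMX survivor mean although the device changes no survivor's stay.

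**4. The same patients on an all-randomised scale.** Take stays counted to day 28, with m between 14 and 20 and e between 22 and 28 days (assumptions), at planned survival. One case is m = 18 and e = 25:

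- Survivor-only PMX mean: (0.65 × 18 + 0.15 × 25) / 0.80 = 19.3 v 18 on control, so PMX looks 1.3 days worse.
- Days alive and out of hospital to day 28, death scored 0: control 0.65 × 10 = 6.50; PMX 6.50 + 0.15 × 3 = 6.95, so PMX looks 0.45 days better.

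Over the whole assumed grid, the survivor-only mean is 0.4 to 2.6 days longer on PMX, while the all-randomised measure favours PMX by 0 to 0.9 days.

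**5. How much true benefit could be masked.** A real reduction r among the other survivors is cancelled when r = (S1 − S0)(e − m) / S0. For m = 18 and e = 25 this is 0.15 × 7 / 0.65 = 1.6 days. Over the grid it runs from about 0.5 to 3.2 days.

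**The case against.** The strongest case on the other side is that stay among survivors is a legitimate descriptive quantity, that the article declares the restriction openly, and that readers will see it beside the mortality result. Item 10 carries no stated power or significance level, and no decision is tied to it. Days alive and out of hospital also answers a different question, because it blends mortality with stay. All of this stands and limits the weight of the point. It does not make the stated between-arm comparison a randomised one. Nor is this a detail left to the analysis plan, since the objective itself fixes the population.

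The size is also open to challenge. The 18.75% needs the full 15-point benefit and a device that causes no deaths. The article does not restate the effect assumed for the resized trial of 650, so 35% v 20% may no longer be the planning case. That is why smaller benefits are shown.

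Three stronger readings are tempting, and the documents do not support them.

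- A reader might infer that an effective device will look as if it prolongs stay. That requires the extra survivors to be sicker and to stay longer. This is plausible in septic shock, but nothing in the article states it.
- A reader might infer that Table 4 contradicts itself, because items 4, 8 and 9 treat death differently. Different summaries for different outcomes are not a contradiction. Those items also do not say that a death scores 0; taken literally, they could credit days before a later death.
- A reader might infer from item 7 ("To compare the effects of two uses of the PMX cartridge on progression of, and recovery from, organ dysfunction") that the organ dysfunction analysis is restricted to patients who reached a second session. Two uses is simply the assigned regimen, as the abstract and the description of the intervention show, and item 7 names no restricted population.

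**Conclusion.** The point holds for item 10 alone. Its comparison of mean hospital days is made in groups defined after randomisation by the primary outcome, and it is unprotected whenever the device changes who survives. If the device does not change who survives, there is no such bias.

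The composition figures follow from the article's planned rates plus the assumption of no device-caused deaths. The bias in days, and its sign, rest on assumed differences in stay: roughly one to two days at planned rates for extra stays of 5 to 10 days, well under one day at 70% survival, and the opposite sign if the extra survivors leave sooner. A larger trial would estimate the biased difference more precisely without removing it.

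The consequence is confined to the interpretation of one secondary or exploratory outcome. It is worth correcting because the correction is cheap.

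**What to change.** Make the between-arm comparison in item 10 the number of days alive and out of hospital from day 0 to day 28 in all ITT subjects. State how deaths are scored (for example, death by day 28 = 0) and apply the same rule to items 4, 8 and 9, where the article leaves it unstated. Report length of stay in survivors to day 28 by arm as a description only, without a test or a claim of treatment effect.

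The change is mainly one of wording in Table 4 and the analysis plan. It has two costs. The new outcome combines mortality with stay, so it must be read beside the mortality result and not as a pure measure of stay. Days back in hospital after a first discharge must also be counted to day 28; the article does not say whether readmissions are recorded, so this may need an extra data item.
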